### Fluoroscopy Time

Total fluoroscopy utilized during the PCI procedure, as recorded by an imaging system.

### Participant and Staff Radiation Exposure

DAP (dose-area-product) and cumulative dose/air kerma, as recorded during the PCI procedure. Radiation exposure to the patient and staff will be measured by personal dosimeters (Polimaster PM1610) placed at the left shoulder.

### Contrast Fluid Volume

Total volume used during the PCI procedure in mLs.

### Equipment utilization (stents, wires, balloons, catheters)

### All equipment used in the PCI will be recorded to perform a cost analysis of technology-assisted PCI versus standard PCI performed by a cardiologist.

## **Lesion Assessment**

The lesion will be measured and recorded by the Cardiologist during the PCI. During the standard care PCI the Cardiologist will measure the lesion as per the institutional procedures. For the technology-assisted PCI the lesion length will be measured with the CorPath GRX System as per the Operations Manual.

The physician will attempt to use the same measuring technique for both pre and post lesion measurements (treatment length and stent length).

A comparison on lesion and PCI device length will be performed:

- 1. Length of segment needing intervention: visual estimate vs. CorPath GRX measurement.
  2. Length of stent(s): manufacturer’s labeled stent length(s) vs. CorPath GRX measurement of implanted stent length(s)

## **Workload assessment survey**

The operator, assistant and nurse involved with the PCI procedure will be asked to complete a survey at the end of the procedure to record an assessment of their workload. This will be via the NASA Task Load Index, which is a survey which assesses workload over 6 domains (mental, physical and temporal demand) [30]. Initially designed for the aerospace industry and NASA, it has been widely utilised and validated across multiple industries [31], including the medical field. It is the most widely cited survey based workload measure [32]

# Study Design

## **Overview**

This is a randomized controlled trial of the CorPath GRX System versus standard PCI to compare participant outcomes at 72 hours post-procedure or hospital discharge, day 30 and 1 year.

The study population will consist of all consecutive participants undergoing PCI at Liverpool Hospital being asked to provide written informed consent prior to PCI and meet the eligibility criteria.

The study will randomize 300 participants equally into the 2 arms:

- Arm 1: PCI using the CorPath GRX System
- Arm 2: PCI using standard care

All enrolled participants will be followed post procedure through hospital discharge or 72 hours, whichever occurs first. The follow up will occur at day 30 and 1 year post-procedure

## **Schema**

Visit 1

Total 300: Perform screening assessment: Obtain written informed consent. Screen potential participants by inclusion and exclusion criteria; obtain history, protocol requirements and document.

Screening

Randomize

Confirm consent

Refer to **Section 3.3 Schedule of Activities**

Perform PCI

Visit 2

Index

Procedure

Visit 3

Refer to **Section 3.3 Schedule of Activities**

Participant discharged

Day 3/Discharge

Visit 4

Follow-up assessments of study endpoints

Refer to **Section 3.3 Schedule of Activities**

Day 30

**Final Assessments**

Refer to **Section 3.3 Schedule of Activities**

Visit 5

End Of Study

## **Schedule of Events**

| **Exam/ Test/ Data Collection** | **Screening** | **Index**  **Procedure** | **Day 3/ discharge** | **Day 30**  **(±5 days)** | **EOS / Day 365**  **(±14 days)** |
| --- | --- | --- | --- | --- | --- |
| Informed consent | X | X |  |  |  |
| Medical history | X |  |  |  |  |
| Demographics | X |  |  |  |  |
| Vital signs including height, weight^1^ | X | X^6^ | X^6^ |  |  |
| Physical examination | X^1^ |  | X |  |  |
| 12 lead ECG | X^4^ |  | X |  |  |
| non-cardiac laboratory assessments | X |  | X |  |  |
| Cardiac enzymes | X^2^ |  | X^3^ |  |  |
| Inclusion/ exclusion criteria | X |  |  |  |  |
| Randomisation |  | X |  |  |  |
| PCI |  | X |  |  |  |
| Dosimeter reading |  | X |  |  |  |
| Fluoroscopy reading |  | X |  |  |  |
| Lesion assessment |  | x |  |  |  |
| Time of procedure |  | X |  |  |  |
| Contrast usage |  | X |  |  |  |
| Equipment usage |  | X |  |  |  |
| Concomitant medications | X | X | X | X | X |
| Adverse Events^5^ |  | X |  |  |  |
| Health care resource usage |  | X | X | X | X |
| Event Assessment |  | X | X^5^ | X^5^ | X^5^ |
| Complete Case Report Form | X | X | X | X | X |

^1^ Within 30 days of index procedure

^2^ Pre-procedure cardiac enzymes within 7 days of index procedure, if collected.

^3^ Post-procedure cardiac enzyme collection is left to the discretion of the investigator and shall be dictated by the participant’s clinical symptoms.

^4^ Post-procedure 12-lead ECG: it is recommended that an ECG be performed at the time of discharge but is not required for the protocol.

^5^ Related to procedure, intervention or Adverse Event of Special Interest (MACE)

^6^ height and weight only required at screening

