**Post Procedure Participant Evaluations**

- Clinical assessment and physical examination
- Record of all adverse events as described in Section 7.7
- If clinically indicated as determined by the investigator
  - 12-lead ECG
  - CK, CK-MB and/or Troponin

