## **Day 3 or Discharge**

The following evaluations are to be performed post the Index procedure on Day 3 or discharge (whichever is sooner):

- Complete physical exam
- Complete vital signs (heart rate, blood pressure)
- Medication assessment
- 12 lead electrocardiogram
  - Blood assays for full blood count, renal function, cardiac enzymes, creatine kinease (CK) & creatine kinease myocardial band (CK-MB) and/or Troponin
- Adverse event assessment as described in Section 7.6
- Event assessment

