# Data Management, Statistical Analysis and Record Keeping

## **Statistical Methods**

This is a double-arm, open-label, randomized controlled trial of the CorPath GRX System designed to evaluate the safety and effectiveness of the clinical and technical performance of the CorPath GRX System in the delivery and manipulation of coronary guidewires and stent/balloon catheters, and remote manipulation of guide catheters for use in PCI in comparison to standard of care. The analysis of data collected as part of the RCT will include, but may not be limited to, the Objectives and Measures outlined in Section 3.0 of this protocol. Continuous variables will be summarized using the number of observations, mean, standard deviation, median, min and max values. Categorical variables will be summarized with the number and percent in each category out of the number observed. Two-sided 95% confidence intervals may be calculated and two-sided p-values < 0.05 will be considered statistically significant.

The outcome of patient radiation exposure will be analysed using variance (ANOVA). As each participant may have multiple lesions, the outcome of clinical success at day 3 will be analysed using a two level multilevel models. Logit link will be used with a binomial distribution and restricted maximum likelihood (REML) will be used for estimation. Predictor variables in the models will include treatment group.

Technical success will analysed with Fisher’s exact test, comparing the proportion of participants with technical success between the two groups. Logistic regression will be used to compare technical success accounting for lesion complexity. For all other secondary outcomes, continuous outcomes will be measured using independent t-test (or non-parametric alternative depending on distributional assumptions), and categorical outcomes analysed by Fisher’s exact test. For outcomes measured repeatedly over time, multilevel models with an appropriate link functions will be used for analysis.

All statistical analyses will be performed using SAS software (version 9.4) or other widely accepted statistical or graphical software.

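### The protocol gives conflicting rules for cardiac enzymes and ECG around PCI and does not say which governs, so detection of biomarker-defined MI may depend on testing chosen by an unblinded investigator

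*Protocol*

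**What the plan says.** Protocol 7.3 opens with "The following evaluations are to be performed post the Index procedure on Day 3 or discharge (whichever is sooner". Its list includes a 12-lead ECG and "cardiac enzymes, creatine kinease (CK) & creatine kinease myocardial band (CK-MB) and/or Troponin", with no discretion clause. Section 7.4 brings same-day-discharge patients back the next day for the review set out in 7.3. Section 7.1 lists the same biomarkers at screening, within 7 days of the procedure.

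The Schedule of Events (3.3) reads differently in its footnotes:

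- Footnote 3, attached to the Day 3/discharge enzyme cell: "Post-procedure cardiac enzyme collection is left to the discretion of the investigator"; it goes on to make symptoms the guide.
- Footnote 4, on the post-procedure ECG: "it is recommended that an ECG be performed at the time of discharge but is not required for the protocol". Its marker stands on the Screening ECG cell; the Day 3/discharge ECG cell has a plain X.
- Footnote 2, on baseline enzymes: "Pre-procedure cardiac enzymes within 7 days of index procedure, if collected".

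Section 7.2.8, on data collection after the procedure, places ECG and biomarkers under "If clinically indicated as determined by the investigator".

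On blinding, 8.1 states "This is a double-arm, open-label, randomized controlled trial". Section 5.3 has the investigator told of the allocation, while the participant is ideally kept blinded.

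**The concern.** The MI definitions in 2.2.1 and 7.7.2 cannot be applied without the tests in question. As the list is laid out, a participant with normal baseline biomarkers meets the definition on post-procedure troponin alone. A participant with elevated baseline needs a rise of more than 20% over the earlier value, plus a supporting finding that may be an ECG change. MI is a component of MACE, and in-hospital MACE is part of clinical success.

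Under the footnotes, symptoms and the investigator's judgement decide who is tested, and the investigator knows the arm. If the threshold for testing differs between robotic and standard PCI, the recorded MI rates differ for reasons unrelated to the procedures, or a real difference is hidden. The events committee (10.2) works from source data supplied by the site, so it can reclassify what was measured but cannot supply a missing troponin. Nor can an analysis plan. Staff also cannot tell from the protocol whether an omitted sample is a deviation.

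**Working it through.** **The texts side by side**

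| Test | Listed as to be done | Contrary text | Direct conflict? |
| --- | --- | --- | --- |
| Enzymes, Day 3/discharge | 7.3 | 3.3 footnote 3, on that same cell | Yes |
| ECG, Day 3/discharge | 7.3, and the unmarked X in 3.3 | 3.3 footnote 4 text | Yes, and 3.3 also disagrees with itself because marker 4 is on the Screening cell |
| Enzymes, baseline | 7.1 | 3.3 footnote 2 | Yes |
| ECG and enzymes after the procedure | 7.3 | 7.2.8 | Not necessarily: 7.2.8 may cover only the acute period |

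No sentence ranks these texts, so two readings remain open.

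**Reading A, 7.1 and 7.3 govern.** Everyone is sampled, and testing cannot differ by arm through investigator choice.

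**Reading B, the footnotes govern.** Testing depends on symptoms and discretion.

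**The protocol's own figure.** The only power statement (8.1) concerns patient radiation. The difference is 0.20 × 1284 = 256.8 mGy. The pooled SD is √((180² + 142.83²)/2) = 162.48, and the standard error is 162.48 × √(2/150) = 18.76. Then z = 256.8/18.76 = 13.69, so power above 99% is reproduced. This point does not touch it. The protocol gives no MI rate and no testing rate.

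**Illustration under Reading B.** All rates here are assumed. Untested participants are assumed to be counted as having no MI, which the protocol does not state.

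1. Testing unrelated to events: observed rate = true rate × proportion tested. With a true rate of 10% in both arms and 90% against 60% tested, 0.10 × 0.9 = 9% and 0.10 × 0.6 = 6%, a ratio of 1.5.
2. Testing partly symptom-led, which is closer to footnote 3. Let a share s of MIs always be tested and the rest be tested at t₁ and t₂. The ratio is [s + (1 − s)t₁] / [s + (1 − s)t₂]. With t₁ = 0.9 and t₂ = 0.6:
   - s = 0: 0.90/0.60 = 1.5
   - s = 0.5: 0.95/0.80 = 1.19
   - s = 1: 1.0
3. False positives, under the simple model in step 1, with 150 per arm, Fisher's exact test and a true rate of 10% in both arms. The probability of p < 0.05 is 3.3% with everyone tested and about 12% with 80% against 50% tested (8% against 5% observed).
4. Masking, same model, true rates 15% against 5%. Power is 79.7% with everyone tested, 40.6% with half of each arm tested (7.5% against 2.5% observed), and 7.2% with 40% tested in the higher-rate arm and 80% in the other (6% against 4% observed).

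These figures show that the mechanism can act in both directions. They do not estimate what would happen in this trial.

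**The case against.** The strongest reply is that 7.3 is plainly the working visit list, since 7.4 relies on it for same-day discharges. On that reading every participant is tested and the footnotes are leftover text. This is a fair reading, but the protocol does not state it, and footnote 3 is attached to the very cell that 7.3 describes.

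Several stronger claims that a reader might infer are not supported:

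- That both tests are symptom-driven. Footnote 4 does not mention symptoms; it only makes the ECG optional, and the unmarked X agrees with 7.3.
- That 7.2.8 is a second direct contradiction. It follows the acute medication regimen and can be read as covering only the hours after the procedure. It needs clarifying.
- That untested participants are scored event-free. The protocol has no such rule, and an analysis plan might address it. Treating them as missing would not remove the difficulty, because missingness would depend on symptoms and on an unblinded choice.
- That the relative risk would be falsely 1.5. That figure needs testing to be unrelated to events, whereas footnote 3 ties it to symptoms.

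Other considerations limit the damage. PCI is done at one hospital, which favours common practice across arms. Participants are meant to be blinded, so symptom reporting should be less affected by allocation. Cardiac death, target vessel revascularisation and residual stenosis need no troponin. None of these fixes who is sampled.

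**Conclusion.** The point stands as a conflict of text with a conditional consequence. Enzymes at Day 3/discharge, ECG at Day 3/discharge and enzymes at baseline are each listed in the visit sections and made optional or conditional in the Schedule footnotes, with no statement of precedence.

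If the footnotes govern, detection of biomarker-defined MI, and through it MACE and clinical success, depends on testing chosen by someone who knows the allocation. The comparison can be biased either way, and the loss cannot be repaired after data collection. If 7.3 governs, this does not arise. The protocol does not establish that bias will occur, and its size and direction cannot be derived from it; the worked figures rest entirely on assumed MI and testing rates. The radiation outcome, the only one with a power calculation, is unaffected.

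The conflict should be resolved because it bears on a main safety measure and a main effectiveness measure.

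**What to change.** Reconcile Schedule footnotes 2 to 4, the placement of marker 4, and section 7.2.8 with sections 7.1 and 7.3. A single endpoint-ascertainment rule for baseline and Day 3/discharge biomarkers and ECG, as 7.1 and 7.3 already list them, should apply identically to both arms. State whether 7.2.8 covers only the acute period. Name the marker that the MI definition needs, since the wording in 7.3 would allow CK-MB without troponin. Leave clinically indicated testing as it is. Report the proportion sampled in each arm beside the MI rate, so that any imbalance in testing is visible.

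The cost is amended text, plus some additional assays and ECGs where staff had been following the footnotes. The sample size and the planned analyses do not change.

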## **End of Study Definition**

A participant is considered to have completed the study if he or she has completed all phases of the study including the last visit or the last scheduled procedure shown in the Schedule of Activities.

The end of the study is defined as completion of the last visit or procedure shown in the Schedule of Activities in the trial.

# Study Population

Participants with coronary artery disease with a clinical indication for PCI and meet the below eligibility criteria will be enrolled into the study.

## **Inclusion Criteria**

- Age 18 to 85 years
- Participants with coronary artery disease with clinical indication for PCI
- Participant deemed appropriate for robotic-assisted PCI
- Able to provide a signed and dated informed consent form

## **Exclusion Criteria**

- The investigator determines that the participant or the coronary anatomy is not suitable for robotic-assisted PCI.

## **Screen Failure**

Screen failures are defined as participants who consent to participate in the clinical trial but are not subsequently randomly assigned to the PCI or entered in the study. All data collected at the screening visit or prior to the time of consent withdrawal will be included in the analysis.

## **Registry of PCIs**

A deidentified registry of all patients undergoing PCI within the Liverpool Hospital cardiac catheterisation lab over the trial period will be kept. Reasons as to why patients did or did not proceed to R-PCI will be recorded.

## **CT and Coronary Angiography Correlation**

A subset of 20 patients undergoing coronary angiogram ± PCI, who have had CT coronary angiograms as part of their workup, will have their anonymised angiogram and CT images compared and correlated by Siemens to improve image quality. The anonymised data will be stored on an encrypted hard drive and then transferred to Siemen’s IT department in Germany using a password protected secure file transfer platform. The data will be stored securely within the Siemens IT server and will be deleted upon completion of the analysis.

## **Strategy for Recruitment and Retention**

All participants who are presenting to Liverpool Hospital for angiography and potential PCI will be asked to participate in this study. Participants will be consented according to Section 11.2 of the protocol.

After the participant has provided consent, the Investigator will confirm eligibility against the inclusion and exclusion criteria. If the participant meets the criteria they will be randomized according to Section 5.3 of the protocol. The participant and their significant others will be blinded to the method of PCI.

Participants will be asked to return for study visits as identified in Section 7. The participant will be contacted prior to the visit to confirm the appointment. If they are unable to attend all efforts will be made to collect the measurements as per the protocol.

If participants withdraws from the study please refer to Section 6.

# Study Intervention

Participants will be randomized to PCI using assisted robotic technology using the CorPath GRX or standard PCI.

## **CorPath GRX**

### Intended Use & Device Description

The CorPath GRX is intended for use in the remote delivery and manipulation of guidewires and rapid exchange balloon/stent catheters, and remote manipulation of guide catheters during percutaneous coronary intervention (PCI) procedures.

The CorPath GRX System is designed to allow the interventional cardiologist to remotely manipulate guidewires, rapid exchange balloon/stent catheters and guide catheters within a participant’s vasculature to perform PCI procedures in a precise and well-controlled fashion, without being exposed to radiation levels typically encountered during a conventional (i.e., manual) PCI. The CorPath GRX System is composed of a Remote Workspace and a Bedside Unit.

### CorPath GRX Remote Workspace

The Remote Workspace consists of a radiation-shielded Interventional Cockpit that houses the Control Console. The Remote Workspace is also designed to integrate a power vision monitor as well as other manufacturers’ angiographic and hemodynamic video monitors, to afford the operator improved visualization of the PCI procedure.

The Control Console component has a touch-screen and three joysticks (one joystick for balloon/stent manipulation, one joystick for guidewire manipulation and one joystick for guide catheter manipulation). The balloon/stent joystick allows for precise control of linear motion (advancement and retrieval) of its respective devices. The guidewire joystick allows for both linear and rotational movement (clockwise and counterclockwise) of the guidewire. The guide catheter joystick allows for precise control of linear motion (advancement and retrieval) and for rotational movement (clockwise and counterclockwise) of the guide catheter. The devices are controlled independently, which allows operations to be performed individually (by using one joystick at a time) or simultaneously (by activating multiple joysticks at once). For precise, discrete manipulation, the balloon/stent, guidewire and guide catheter can also be manipulated in discreet 1-mm increments via the touch-screen buttons on the Control Console.

### CorPath Bedside Unit

The Bedside Unit consists of three components: (1) Extended Reach Arm, (2) Robotic Drive and (3) single-use Cassette (“Cassette”). The Extended Reach Arm supports the Robotic Drive, which houses the Cassette. The joysticks on the Control Console remotely deliver signals through a communication cable to the Robotic Drive that operates the Cassette. After the selected guidewire and catheter are loaded into the Cassette, the Cassette translates the signals from the joystick manipulations into the linear and rotational movements of the guidewire and guide catheter and the linear movements of the balloon/stent. The Cassette has a Y-connector holder which holds the guide catheter hub and is attached to the drive gear and CoPilot. The drive gear enables guide catheter rotation.

The CorPath GRX System sub-units function together via a Communication Cable. The CorPath GRX System utilizes proprietary software that is designed to operate within the parameters that have been proven to execute precise motion and movement of guidewires, balloon/stent systems and guide catheters within a blood vessel.

***Note: For a more detailed description of the CorPath GRX please refer to the CorPath GRX System Operator’s Manual.***

## **Storage and Accountability**

The investigator is responsible for device accountability at the study site. The investigator may delegate some of the investigator’s duties for device accountability at that site to an appropriate staff member. All devices provided by the Ingham Institute for Applied Medical Research will be stored in a secure and locked area at the site.

The investigator must maintain records that document device delivery to the study site, the inventory at the site, administration to each participant, and submit required forms to the appropriate authority if requested. These records include at a minimum date (received, used, returned), quantities, lot/serial numbers, and expiration dates assigned to the study device and the participant’s identification code, if used. Study devices must be recorded on the Device Accountability Log. The investigator must notify the appropriate authority of any damaged or unusable devices that were supplied to the site.

